## Methods

### Study design

This is a two-phase study:

*Phase 1*: We will develop an exercise rehabilitation education program for post-PCI patients based on the message framing effect through qualitative needs assessment, evidence synthesis, and expert consensus.*Phase 2*: We will conduct a prospective, parallel-controlled, single-blind randomized controlled trial using a 2 (gain vs. loss framing) × 2 (narrative vs. non-narrative framing) factorial design to implement the exercise rehabilitation education program, comprising four groups: Group A (gain-narrative framed message), Group B (loss-narrative framed message), Group C (gain-framed non-narrative message), and Group D (loss-framed non-narrative message). This phase includes a 3-week intervention period and a 3-month follow-up period. The study design is shown in Figure 1.

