### Patients

Patient recruitment will be managed by experienced clinical nurses. Before recruitment, these nurses will receive comprehensive training from the research team on the study’s objectives, methods, and procedures. Leveraging their familiarity with the patients’ specific conditions, the nurses will ensure a professional and efficient recruitment process. Following recruitment, a member of the research team will provide a standardized explanation of the study’s purpose and significance to all participants. Special emphasis will be placed on the confidentiality agreement, explicitly instructing patients not to discuss the intervention details with other participants. This process is designed to address patient concerns, enhance intervention adherence, and ensure the integrity of the trial. The researcher will assure participants that their personal information will remain strictly confidential and will be used solely for scientific research and publication. It will be clearly stated that participants can withdraw from the study at any time without penalty or consequence. Written informed consent will be obtained from all eligible participants before any data collection. Table 1 displays the patient inclusion and exclusion criteria, as well as shedding details.

**Table 1 tab1:** Patient inclusion, exclusion and shedding criteria.

Criteria	Content
Inclusion criteria	Patients who have undergone PCI; Patients aged greater than or equal to 18 years; Stable condition post-surgery, with no severe cardiovascular complications; Patients assessed as low-risk for exercise rehabilitation post-PCI according to the *Expert Consensus on Exercise Rehabilitation After Percutaneous Coronary Intervention;* Patients can manipulate a smartphone with WeChat independently, or have a co-residing primary caregiver (who fulfils these technical criteria) to assist them;
Exclusion criteria	Individuals with physical mobility impairments; Malignant tumors or other serious complications; Pregnant or breastfeeding individuals; Mental illness, cognitive impairments, or language communication barriers; Individuals currently participating in other studies;
Shedding criteria	Voluntary withdrawal from the study; Loss to follow-up; Participants failing to complete the video-based intervention as required; The occurrence of any serious adverse event or a significant deterioration in health status during the trial period;

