### Sample size

The primary outcome indicator adopted in this study is exercise adherence. The sample size was calculated using the sample size estimation formula for multiple means in randomized controlled trials, accounting for a 20% dropout rate, resulting in a final sample size of 100 subjects. The sample size calculation was determined using PASS 2021 software.

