1 week after discharge	Aerobic exercise guidance	Gain frame	Loss frame	Gain frame	Loss frame	WeChat
2 Weeks after discharge	Resistance exercise guidance	Gain frame	Loss frame	Gain frame	Loss frame	WeChat
3 Weeks after discharge	Flexibility exercise guidance	Gain-narrative frame	Loss-narrative frame	Gain frame	Loss frame	WeChat

During the intervention period, patients in all four groups can continue to receive their regular medical treatment and rehabilitation management (e.g., medication, dietary adjustments, psychological support, etc.), which are assessed to be compatible with the intervention content of this trial and are not expected to affect the effectiveness of the intervention. If patients need to receive other treatments (e.g., surgery, emergency treatment, etc.) or adjust their routine treatment due to health problems during the trial period, the research team will assess whether these treatments affect the efficacy and credibility of the findings of the trial and decide whether participants can continue to participate in the study. In addition, any additional treatments or medications other than routine treatment will be reported to the research team in advance and will be evaluated by the research team as appropriate to ensure that they do not adversely affect the trial intervention.

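### The rule on other treatments lets a research team not stated to be blinded take randomised patients out of the study, with the effect on the findings as the only named ground

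*Protocol article*

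**What the plan says.** The rule stands in the Interventions section of the protocol article, in the paragraph after Table 2.

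- **Trigger:** other treatment, or a change of routine treatment, described as "surgery, emergency treatment, etc.) or adjust their routine treatment due to health problems during the trial period".
- **Decider and ground:** the research team is to "assess whether these treatments affect the efficacy and credibility of the findings of the trial and decide whether participants can continue". The following sentence, on additional treatments, again asks only about their effect on the trial intervention.
- **Consequence:** the team is to "decide whether participants can continue to participate in the study". The decision is about the study, not only about the videos.

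Other parts of the article bear on the same patients:

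- Table 1 (Patients section) lists as a shedding criterion "The occurrence of any serious adverse event or a significant deterioration in health status during the trial period". Among its entry conditions is "Patients assessed as low-risk for exercise rehabilitation post-PCI".
- Study design calls the trial a "prospective, parallel-controlled, single-blind randomized controlled trial", and the blinding section names only the participants as blinded.
- Ethics and dissemination ends only the relevant part of participation, after a physician has evaluated the patient, but this applies to harm directly related to study procedures.
- Data statistics and analysis fits a linear mixed model by maximum likelihood to all available data.

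**The concern.** A patient's place in a randomised comparison should not depend on whether keeping that patient is thought good or bad for the results. This rule makes exactly that the test, and it applies it after randomisation, at the team's discretion, to patients who have just had a health problem. Such problems plausibly relate to exercise adherence, the primary outcome, so the removals could be informative. Nothing stated keeps the deciding team unaware of the group.

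Removal from the study also costs outcome data. The mixed model can use whatever is collected, but it cannot use a questionnaire that was never sought. Its validity with incomplete data rests on missingness being at random, which selective removal can break.

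There is a smaller clinical side. Entry requires low exercise risk, yet the rule does not ask whether that still holds after the new treatment.

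**Working it through.** **1. Which rule governs which patient**

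| Event | Rule that applies | Ground named |
|---|---|---|
| Serious adverse event or significant deterioration | Table 1, shedding | Health |
| Injury or deterioration directly related to study procedures | Ethics and dissemination | Physician evaluation; relevant part only |
| Other treatment or treatment change for health reasons, below Table 1's threshold and not study-related | Interventions | Effect on the findings only |

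The first two rows have a health-based ground. The third has none. Where the first and third overlap, the article does not say which comes first, but reading Table 1 first is natural and nothing contradicts it.

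**2. What removal costs, by time**

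Study design states: "This phase includes a 3-week intervention period and a 3-month follow-up period". Taking 3 months as about 13 weeks and 1 month as about 4 weeks, counted from the end of the intervention:

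- 1-month post-intervention visit: 3 + 4 = about week 7.
- 3-month post-intervention visit: 3 + 13 = about week 16.

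| Time of removal | Exercise videos still due | Follow-up questionnaires lost |
|---|---|---|
| Before the week-1 video | 3 | 2 of 2 |
| Between the week-1 and week-2 videos | 2 | 2 of 2 |
| Between the week-2 and week-3 videos | 1 | 2 of 2 |
| Week 3 to about week 7 | 0 | 2 of 2 |
| About week 7 to about week 16 | 0 | 1 of 2 |

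After week 3 no video is left to stop, so removal then can only cost outcome data. That period is 13/16 = 81% of calendar time. It is not 81% of events, because the article gives no event timing.

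**3. Dropout allowance**

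Sample size states: "accounting for a 20% dropout rate, resulting in a final sample size of 100 subjects". The allowance is 0.20 × 100 = 20 patients, and 80/(1 − 0.20) = 100 agrees with 80 evaluable. Each removal uses one of those 20 places.

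**4. Possible bias**

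No event rate is given, so these inputs are assumptions: k = 1 to 4 patients removed, all from one level of one framing factor, with outcomes d = 0.5 to 1 SD away from the rest. Under 1:1:1:1 simple randomisation of 100, the expected sizes are 50 per framing level and 25 per group.

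The shift in a mean when k of n such patients are removed is k × d / n.

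- Main effect, n = 50: lowest 1 × 0.5 / 50 = 0.01 SD; highest 4 × 1 / 50 = 0.08 SD.
- Single group, n = 25: lowest 1 × 0.5 / 25 = 0.02 SD; highest 4 × 1 / 25 = 0.16 SD.

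The standard error of a main effect at one visit is √(2/50) = 0.20 SD, or √(2/40) = 0.22 SD after 20% dropout. The main-effect shift is therefore at most 0.08/0.20 = 0.4 of a standard error. If removals are alike in number and kind across groups, the shift in the contrast is zero and only data are lost.

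**The case against.** The strongest reply is that this is a clause on concomitant treatment, not the trial's safety rule, and that safety is handled elsewhere. Table 1 sheds on any serious adverse event or significant deterioration, whether or not it is study-related. The videos list contraindicated exercises and stop signals, and patients are told what to do if they feel unwell. Study-related harm goes to a physician. Most of this stands. A reader might infer that a patient could be sent the next exercise video after a serious event because the findings were judged unaffected. The documents do not support that: it would need this clause to override Table 1, and nothing says it does. What remains is the lesser event or treatment change, in the first three weeks only, for which contraindications and stop signals reduce the risk but do not re-check suitability.

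A second reply is that the article does not say collected data are discarded, and that analysis sets and follow-up after discontinuation are commonly left to the full protocol. That is fair as far as it goes. The inference that questionnaires stop comes from the wording that the decision concerns participation in the study. It is the natural reading, but it is an inference.

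Third, a reader might infer that the team would remove patients knowing their group, or that the result would be seriously biased. Neither is shown. The clause names the research team, while a researcher sends the weekly videos. That the deciders know the group is possible but not stated. The bias figures are small, they rest on assumed inputs, and the losses would sit within the planned dropout allowance.

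None of this repairs the rule itself. The article prints a trigger, a decider and a ground, and the ground is the wrong one. This is not detail left to another document.

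**Conclusion.** The point holds as a flaw in a stated rule. The main problem is discretionary, possibly informative removal after randomisation and loss of outcomes that need not be lost. The safety gap is secondary and confined to events and treatment changes that Table 1 does not reach.

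The case for change does not rest on a large bias. The calculated shift in a main effect is well below one standard error even when every removal is assumed to fall on one framing level. That range depends on the assumed number of removals and outcome gap, and on the expected group sizes. The data-loss counts depend on reading removal from the study as ending its questionnaires, and on counting the follow-up visits from the end of the three-week intervention. The rule should be changed because its criterion is unsound, the loss is avoidable and the correction is cheap.

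**What to change.** Two linked edits are needed.

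1. **Interventions.** When a patient needs other treatment or a treatment change, let continuation of the videos depend on a physician's judgement, for example the treating physician's, that exercise is still suitable. Remove the expected effect on the findings as a ground. State that stopping the videos does not end follow-up.
2. **Table 1.** Change the shedding criterion on serious adverse events and deterioration so that it stops the intervention only. Without this edit, the same serious event would shed the patient under Table 1 and keep the patient in follow-up under Interventions.

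In both cases, still seek the 1-month and 3-month questionnaires unless the patient withdraws, and analyse them as randomised in the planned mixed model. The Ethics and dissemination section already has the right form, with physician evaluation and stopping only the relevant part, so the change extends an existing principle.

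The cost is a few sentences in two places, a clinical judgement for the few patients affected, and some added outcome noise from retained patients who had co-treatment. No patients or visits are added.

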### Data collection and outcomes

Data will be collected at baseline before intervention, 1-month post-intervention, and 3-month post-intervention. At baseline, paper questionnaires will be distributed on the day of discharge before the first video viewing to collect data; at 1-month and 3-month follow-up, online questionnaires will be completed via Questionnaire Star. For those unable to complete the survey via Questionnaire Star, telephone follow-ups will be conducted. The questionnaires will be distributed and collected by trained researchers. The assessment tools used need to be fully validated and selected for their established reliability and validity in the original study, ensuring accuracy and comparability. In the process of completing the questionnaire, the researcher will answer the subjects’ questions on time, check for missing items after completing the questionnaire, and instruct the subjects to add a message as needed. After data collection is completed, the data will be entered promptly. Following data entry into the analysis system, independent double data checks will be performed by two researchers to ensure accuracy. This trial is a low-risk, non-pharmacological behavioral intervention; therefore, a formal DMC will not be established.

The assessment of general patient message, designed by the study team itself through literature review and group discussion, will be divided into 2 parts. Part 1 will be general demographic message, including gender, age, ethnicity, religious beliefs, literacy, marital status, mode of residence, occupation, monthly household income, and type of health insurance; part 2 will be disease-related information, including duration of coronary heart disease, current diagnosis, medication use and types of medication, comorbidities, and a history of acute myocardial infarction or cardiac surgery.

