### Interventions

The intervention content of this study will be based on the exercise rehabilitation education program. On the day of discharge, researchers will select a quiet private departmental meeting room and use a time-slot booking system to ensure that the four participant groups do not overlap. We will explain the purpose, methods and procedures of the intervention to patients face-to-face and implement the first intervention. Educational videos will be sent to participants via WeChat for viewing and learning, serving as the primary form of the intervention. Participants will be guided through the video-viewing process, and after viewing, they will be asked questions regarding the basic content presented in the video. If the patients are unable to recall the content, the video will be replayed until the patients indicate they understand the content. During the viewing period, any questions raised by the patients will be promptly addressed.

In weeks 1, 2 and 3 after discharge, the researcher will remind patients to watch the video after sending the corresponding study content and video every week. After viewing, participants will be invited to answer two brief questions related to the video content. The researcher will also maintain continuous communication with participants and will promptly address any questions raised during the study period. After completing each video study and test, patients will be praised and encouraged via WeChat to improve adherence. The four groups will receive different contents of short educational videos, but the mode, timing, and frequency of video delivery and question prompts are the same across groups. The health education content provided by medical staff during hospitalization and in routine post-discharge follow-up is also identical. In this study, scientifically validated exercise instruction videos will be provided, clearly listing contraindicated exercises and emergency stop signals. We will inform patients of the procedures to be followed in case of discomfort during exercise to ensure patient safety. The process of intervention implementation can be seen in Table 2.

**Table 2 tab2:** Process of implementation of the exercise rehabilitation education program.

Intervention time	Video theme	Frame				Intervention implementation
		Group A	Group B	Group C	Group D	
On the day of discharge	Post-PCI exercise rehabilitation education	Frameless	Frameless	Frameless	Frameless	Face-to-face, WeChat

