#### Primary outcome

The primary outcome indicator is patient exercise adherence. We will use the Exercise Adherence Scale developed by Weng (35) to assess patients’ exercise adherence. The scale contains 15 entries divided into three dimensions covering exercise adherence, exercise monitoring adherence, and actively seeking advice. The higher the total score of the scale, the better the patient’s exercise adherence.

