### Design justification and constraints

This study employs a 2 (gain vs. loss framing) × 2 (narrative vs. non-narrative framing) factorial design, which is relatively novel in the field of post-PCI patient exercise rehabilitation education. This design allows the researcher to test the independent effects of two or more factors at the same time, and more importantly, it can analyze whether there is an interaction effect between the different levels of these factors, i.e., whether the effect of one factor is dependent on the level of another factor. This means the design can not only obtain the message on the main effects of each factor, but also find out whether the factors act synergistically, antagonistically, or independently of each other, thus greatly improving the message output and experimental efficiency of the study, and avoiding the large amount of resources and time costs required to conduct single-factor experiments in multiple trials. It can further validate the unique value of the message framing effect in exercise rehabilitation education and provide new insights for future theoretical development in this field. The absence of a control group receiving conventional education means that we cannot directly determine if the message-framing interventions are superior to standard educational practices. To address this design limitation, this study strictly adopts a pre-post comparison format. Based on this, future studies may consider setting up a blank control group, where the control group receives routine exercise rehabilitation education without specific message framing interventions. By comparing the results of the intervention group with those of the blank control group, the effectiveness of the message framing intervention can be more accurately assessed, while eliminating other confounding factors, thereby enhancing the scientific rigor and reliability of the study conclusions.

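### Exercise adherence, the primary outcome, appears to be scored at discharge before the study's exercise teaching, so its pre-post change does not track one quantity and cannot stand in for a control

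*Protocol article*

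**What the plan says.** In the protocol article, Data collection and outcomes sets the schedule: "Data will be collected at baseline before intervention, 1-month post-intervention, and 3-month post-intervention". It then places the first of these assessments: "At baseline, paper questionnaires will be distributed on the day of discharge before the first video viewing to collect data".

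Primary outcome names the endpoint, "The primary outcome indicator is patient exercise adherence", and describes the instrument: "The scale contains 15 entries divided into three dimensions covering exercise adherence, exercise monitoring adherence, and actively seeking advice". It gives no recall period or reference regimen.

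Table 2 under Interventions shows when the study's own teaching starts. The first row reads "On the day of discharge Post-PCI exercise rehabilitation education Frameless Frameless Frameless Frameless Face-to-face, WeChat". The first framed guidance comes a week later: "1 week after discharge Aerobic exercise guidance Gain frame Loss frame Gain frame Loss frame WeChat". Resistance and flexibility guidance follow in weeks 2 and 3.

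Data statistics and analysis specifies a linear mixed model with the two framings and time as fixed effects and participant as a random effect. It tests all main effects and interactions and does not treat adherence differently from the other outcomes.

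Design justification and constraints concedes that there is no conventional-education arm and continues: "To address this design limitation, this study strictly adopts a pre-post comparison format".

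**The concern.** Adherence describes how far someone follows an exercise programme. On the day of discharge, before the first video, a patient has had no home exercise period after this admission and none of the study's teaching. A score taken then refers to a different period, and possibly a different regimen, from the scores at 1 and 3 months.

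Two things depend on that score. The time effect, and the pre-post comparison offered in place of a control, would be read as improvement in adherence. In addition, if baseline is one of three levels of time, the framing tests either subtract it (framing by time) or average over it (framing main effect). Both bring a pre-treatment value into the primary comparison, and that value may be only weakly related to later adherence.

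The problem is separate from the lack of a control arm, because the adherence baseline would refer to something else even if a control arm existed. It is also largely specific to the primary outcome: intention, fear of exercise and self-efficacy can sensibly be answered at discharge.

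**Working it through.** **Is the scale given at baseline?** The article has no instrument-by-visit list. The Abstract applies the mixed model to primary and secondary outcomes across multiple time points, Data collection and outcomes lists three assessments, and the analysis section makes no exception. Baseline use of the scale is therefore a strong inference, not a stated fact.

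**What can each score refer to?**

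| Assessment | Study exercise teaching so far | Home exercise since this admission |
|---|---|---|
| Discharge, before first video | none | none |
| 1 month | complete (weeks 1 to 3) | yes |
| 3 months | complete | yes |

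The first row differs in kind from the other two, so the baseline-to-follow-up difference mixes the move from hospital to home with any effect of the videos.

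**Inputs for the cost in precision.**
- Total 100 with 20% dropout (Sample size). The dropout step is consistent with 80 evaluable: 80/(1 − 0.20) = 100. The 80 itself cannot be reproduced, because the article gives no effect size, SD or power.
- Allocation 1:1:1:1, hence 40 v 40 evaluable for each framing factor. Two-sided alpha 0.05.
- Assumed: equal SD at each visit; baseline-to-follow-up correlation ρ of 0, 0.2 or 0.3; correlation 0.6 between the two follow-ups; an effect of 0.63 SD at both follow-ups and none at baseline. The documents give none of these.

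Power = Φ(effect/SE − 1.96).

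**Framing contrast at one visit.**
- Follow-up alone: SE = √(2/40) = 0.224 SD; 0.63/0.224 = 2.82; power 80%.
- Change from baseline: SE = √(2 × 2(1 − ρ)/40).

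| ρ | SE (SD) | Wider than follow-up alone | Power |
|---|---|---|---|
| 0 | 0.316 | 41% | 51% |
| 0.2 | 0.283 | 26% | 61% |
| 0.3 | 0.265 | 18% | 66% |
| 0.5 | 0.224 | 0% | 80% |

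The two break even at ρ = 0.5.

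**Framing main effect averaged over visits.**
- Over three visits, the null baseline dilutes the effect to 2/3 × 0.63 = 0.42 SD. The variance of a patient's mean is [3 + 2(0.6 + 2ρ)]/9.
 - ρ = 0: variance 0.467, SE = √(0.467 × 2/40) = 0.153, power 79%.
 - ρ = 0.2: variance 0.556, SE 0.167, power 71%.
- Over the two follow-ups only: variance (2 + 2 × 0.6)/4 = 0.80, SE = √(0.80 × 2/40) = 0.200, power 88%.

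**Baseline as a covariate.** The variance factor is 1 − ρ², so the effect detectable with 80% power is 0.63, 0.60 and 0.54 SD at ρ = 0, 0.3 and 0.5. Follow-up alone gives 0.63 SD. Adjustment therefore loses essentially nothing if the discharge score is uninformative, and gains if it is informative.

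**The case against.** The strongest reply is that the documents do not show the baseline to be empty. Interventions mentions health education by medical staff during the hospital stay. Table 1 does not require a first PCI. Duration of coronary disease and previous infarction or cardiac surgery are recorded, so some patients may bring earlier exercise advice. The items and recall period of the scale are not shown, and monitoring and advice-seeking may be answerable at discharge. All of this stands. A reader might infer that no patient has any adherence to score, or that every score sits at the floor and makes the time effect significant by construction; the documents support neither. They also do not support reading the check for missing items as an order to fill in inapplicable answers, since patients are asked to add information only as needed.

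The randomised comparison also survives. The baseline problem is common to all four groups, so framing differences at 1 and 3 months remain valid. The article itself admits that superiority over standard education cannot be determined.

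Finally, the 51% to 66% figures describe a raw change score, not the planned model. In 300 simulated trials of a random-intercept model with baseline as a time level, the 3-month framing-by-time contrast had power 0.59 at ρ = 0 and 0.66 at ρ = 0.2, against 0.79 for the 3-month comparison alone. The loss is milder but still present. The precision loss also presumes a baseline with full spread; if most patients did score near the floor, it would be small.

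What the reply does not rescue is the pre-post reading. A patient with earlier exercise habits is still reporting on a different period, and mixing such patients with newcomers makes the baseline harder to interpret.

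**Conclusion.** The point holds for the pre-post reading and for precision; it does not touch the validity of the randomised comparison. As the plan stands, the time effect on adherence and the pre-post comparison do not measure change in one quantity. A rise is expected regardless of the videos and cannot substitute for a control.

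Under the assumptions listed, keeping the discharge score as a level of time takes power from 80% to about 51% to 66% for a change contrast at one visit (ρ from 0 to 0.3). For a main effect averaged over visits, it takes power from 88% to about 79% (ρ = 0) or 71% (ρ = 0.2). These figures illustrate the size of the loss and do not predict it, because the documents give no SD, effect size or correlation. The conclusion about interpretation does not depend on them. It rests on the stated timing and on the inference that the adherence scale is among the baseline questionnaires.

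**What to change.** For exercise adherence only:

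1. Take the 1- and 3-month scores as the outcome in the mixed model and test the framing contrasts there.
2. Use the discharge-day adherence score, if collected, only as a covariate, together with the intention, TSK-Heart and CESEI scores if these are collected at discharge.
3. Make no pre-post effectiveness claim for adherence, and withdraw the statement in Design justification and constraints that the pre-post format addresses the missing control.

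The three-time-point analysis can stay for secondary outcomes that are answerable at discharge. Rewording the scale or adding a not-applicable option is not needed, and would alter an instrument chosen for its validation.

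The change is to wording in the analysis and discussion sections, with no extra patients, visits or staff. The downside is that the trial can no longer report a pre-post rise in adherence. If the discharge score turns out to predict later adherence well, the covariate adjustment still uses that information.
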